### Bias

With the use of the consensus definition a homogeneous population should be guaranteed although research in the more severe cases of paratonia indicates that if the resistance in affected limbs is very high the assessor is not able to accelerate the movement and adequate differentiation with Parkinsonian (lead pipe) rigidity becomes impossible [6]. Furthermore, we did not specify the type of dementia in the inclusion criteria. At this moment we know that in the advanced stages of the disease all patients have paratonia. However, it is unclear if there are any dissimilarities in the development and severity of paratonia in different types of dementia. Therefore paratonia, diagnosed in different dementias, could react inconsistently to PMT and although we take this into account in our analysis this uncertainty could be a potential source of bias.

With this study, we hope to clarify the effect of passive movement therapy on moderate to severe paratonia and hopefully gain some scientific basis for the use of this treatment or to abandon PMT in this population. The controversy between the hypothesis of the research team that PMT is possibly harmful and the assumption of nurses and relatives that it is beneficial, necessitates a thorough organisation for keeping all assessors blind for treatment allocation. Therefore randomisation is done in a block size randomisation system with block size of four. For each participating nursing home a new sequence is calculated at the faculty of Epidemiology of the Maastricht University. The blinding of the assessors can be compromised by an incidental verbal hint of one of the participants although most of the participants are in the advanced stage of dementia and lost there capacity of speech.

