**Methods/Design:**

A RCT with a 4-week follow-up period. Patients with dementia (according to the DSM-IV-TR Criteria) and moderate to severe paratonia are included in the study after proxy consent. By means of computerised and concealed block randomisation (block-size of 4) patients are included in one of two groups. The first group receives PMT, the second group receives usual care without PMT. PMT is given according to a protocol by physical therapist three times a week for four weeks in a row. The severity of paratonia (Modified Ashworth scale), the severity of the dementia (Global Deterioration Scale), the clinical improvement (Clinical Global Impressions), the difficulty in daily care (Patient Specific Complaints) and the experienced pain in daily care of the participant (PACSLAC-D) is assessed by assessors blind to treatment allocation at baseline, after 6 and 12 treatments.

Success of the intervention is defined as a significant increase of decline on the modified Ashworth scale. The 'proportion of change' in two and four weeks time on this scale will be analysed. Also a multiple logistic regression analysis using declined/not declined criteria as dependent variable with correction for relevant confounders (e.g. stage of dementia, medication, co-morbidity) will be used.

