### Patients

The study population consists of patients with dementia (according to the DSM-IV-TR Criteria) and established paratonia according to the Paratonia Assessment Instrument (PAI). The PAI is a construct of five criteria derived from the definition, representing distinct elements of the clinical manifestation of paratonia [6]. The resistance felt during passive movement due to paratonia has to be at least in one of the limbs more marked i.e. a score of 2 or more on the modified Ashworth scale. Possible participants will be identified by trained personnel of participating nursing homes. After identification of participants the researcher checks if the patient is eligible for the study and if so will contact the legal representative(s) of the patient by sending an information leaflet about the study. Patients are only included after proxy consent. Because patients are included after proxy consent we will exclude participants who indicate during the trial in any way, verbally or nonverbally, not to approve of participation. Patients with an unstable disease, as judged by the nursing home physician, such as progressive malignant cancer or other diseases with an obvious progressive negative effect on the motor function or health status are excluded as well as patients who received passive movement therapy within a period of 4 weeks prior to admission or who receive typical or a-typical antipsychotics.

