### Interventions

Patients are included in one of two groups after computerised and concealed block randomisation (block size of four). The first group receives usual care with PMT, the second group receives usual care without PMT. Usual care generally consists of grooming and dressing with slow and gentle movements by trained nurses. Some of the participants wear especially designed clothing that enables the nurses to dress patients more easy while the patient is lying in bed or sitting in a wheelchair. Most participants use cushions, mostly manufactured on demand, for a stable position in bed and sit during the day time in comfortable wheelchairs.

PMT is provided in a standardized way. During the first part of passive movement the therapist moves slowly the affected limbs, with the emphasis on lowering the resistance. After this, the therapist tries to reach the end range of motion and possibly stretches the structures very lightly without causing pain. The patients are positioned comfortably supine in bed while the therapist starts PMT with the left arm moving it in flexion and extension (up and down). Subsequently PMT is performed on the right arm, left leg and finally the right leg. The duration of PMT is approximately 20 minutes per patient per session. The treatment group receives PMT, between 8 a.m. and 10 a.m., shortly before being washed and dressed by nursing staff, three times a week for four weeks in a row. In order to safeguard blinding of the assessors for treatment allocation, the control group receives a placebo treatment in the same frequency and in the same time frame. The patients of the control group are positioned comfortably supine in bed after which the therapist stays in the room for approximately 20 minutes. On every treatment day a special signboard on the participant's bedroom door indicates that research is going on advising nursing staff to delay their activities with the participant and not disturb the treatment session.

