### validity

The research will be conducted in four different nursing homes, that will enhance extrapolation of study findings. However, due to the fact that at least 4 different geriatric physical therapists will perform PMT and at least two different assessors of the severity of paratonia will participate, the internal validity may become compromised. A protocollized way of performing PMT and an extensive training of all therapists and assessors involved should ensure internal validity of this study and reliability of assessed outcomes.

The results of this randomised controlled trial will be published in a scientific journal and will be used for recommendations in the guideline of geriatric physical therapy and implemented in current physical therapy practice. This guideline will be developed according to method of clinical practice guideline development of the Royal Dutch Physiotherapy Association (KNGF) [21].

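### A fixed block of four per nursing home is offered as a blinding measure, but it blinds nobody and makes allocation easier to predict

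*Protocol article*

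**What the plan says.** The Bias section of the protocol article contrasts the research team's suspicion that PMT is harmful with the expectation of nurses and relatives that it helps. It says that this conflict "necessitates a thorough organisation for keeping all assessors blind for treatment allocation", and draws the consequence: "Therefore randomisation is done in a block size randomisation system with block size of four". The next sentence adds: "For each participating nursing home a new sequence is calculated at the faculty of Epidemiology of the Maastricht University". The only threat to assessor blinding that the section names is a remark by a participant.

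The Abstract and the Interventions section also give the block size as four and describe the allocation as concealed. No variation in block size is mentioned anywhere.

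Three other statements bear on the point:
- Interventions: the therapist either performs PMT or, for controls, only stays in the room for about 20 minutes. The therapist therefore knows the arm of each patient treated.
- Validity: "The research will be conducted in four different nursing homes", and "at least 4 different geriatric physical therapists will perform PMT".
- Patients: "Possible participants will be identified by trained personnel of participating nursing homes". The researcher then checks eligibility.

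**The concern.** The inference in the Bias section does not follow. Permuted blocks keep the arms close in size; they do not prevent an assessor from learning an allocation. A small block of constant, stated size works in the opposite direction, because the allocations already made in a block restrict those still to come. With a separate sequence per home, the predictable unit is the home, where the people who deliver the treatment know the arms.

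Two things could be affected. First, concealment: someone who can foresee the next allocation could, in principle, influence who is put forward and when. Second, blinding: if one patient's arm becomes known, the block structure gives information about the others in that block. The primary outcome, the Modified Ashworth score, is a rating of felt resistance, so it is open to influence if a rater suspects the arm.

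**Working it through.** **Inputs.** Block size 4, with one sequence per home (Interventions, Bias). Four homes (validity). 69 patients per group (Sample size), so 2 × 69 = 138 in total. Equal group sizes imply 1:1 allocation, so each block holds 2 PMT and 2 control. The article gives no figure for predictability.

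**The plan's own figure.** For 30% against 10%, two-sided alpha 0.05, 80% power and no continuity correction:

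n = [1.960 × √(2 × 0.2 × 0.8) + 0.842 × √(0.3 × 0.7 + 0.1 × 0.9)]² / 0.2² = 61.6, rounded up to 62.

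Allowing for 10% drop-out, 62 / 0.9 = 68.9, rounded up to 69. The stated 69 reproduces, and block size does not affect it.

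**Determined allocations.** There are 6 equally likely orders of 2 + 2. Suppose a person knows all earlier allocations in the home and where each block starts.
- Places 1 and 2 are never certain.
- Place 3 is certain when the first two are alike: 2 of 6 orders, or 1/3.
- Place 4 is always certain.

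The expected number per block is 1/3 + 1 = 4/3, and (4/3) / 4 = 1/3. Over complete blocks, 138 / 3 = 46 patients.

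**Best guessing.** The chance of being right at places 1 to 4 is 1/2, 2/3, 2/3 and 1. The mean is (1/2 + 2/3 + 2/3 + 1) / 4 = 17/24 = 70.8%, against 50% under simple randomisation.

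**Incomplete last blocks.** 138 / 4 = 34.5, so assume about 35 patients per home (the article does not give the split). That is 8 complete blocks and 3 further patients: (8 × 4/3 + 1/3) / 35 = 11/35 = 31.4%. This is why 46 is an upper figure.

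**After one leak.** If one patient is known to receive PMT, the other three places in the block hold 1 PMT and 2 controls. Each of those patients is then a control with probability 2/3 instead of 1/2.

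**Alternatives.** These were simulated with 35 patients per home. The guesser knows all earlier allocations and the set of possible sizes, but not the size drawn for each block.

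| Block sizes | Certain | Best guess right |
|---|---|---|
| fixed 4 | 31.5% | 69.9% |
| 4, 6 | 5.7% | 68.6% |
| 2, 4, 6 | 3.7% | 69.6% |
| 4, 6, 8 | 2.4% | 67.3% |

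Varying the size removes nearly all certain allocations. It lowers best-guess accuracy only slightly.

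**The case against.** A reader might infer that a third of this trial's allocations are known in advance to people who choose the patients, and that the primary comparison is therefore biased beyond repair. The article does not support that.

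- The one-third figure is conditional. It needs knowledge of every earlier allocation, the enrolment order and the block boundaries in a home. At least four therapists in four homes is compatible with one per home, but that is not stated.
- Knowledge and opportunity are not placed in the same person. Therapists know arms but are given no part in enrolment. Whether the personnel who identify candidates include therapists is not said, nor is whether the researcher sees earlier allocations. The expectation of benefit is attributed to nurses and relatives, not to staff in general.
- There are safeguards. Sequences are produced outside the homes, and allocation is described as concealed. Controls get a placebo session of the same frequency and timing, expressly to protect assessor blinding. The Ashworth rating is made on a different day from treatment.
- The 2/3 figure needs an assessor to know which patients share a block, and nothing says that assessors see enrolment order.
- The outcome is change from each patient's own baseline, and the planned logistic regression adjusts for age, sex, and severity and type of dementia. That can reduce imbalance on measured factors, though not on unmeasured frailty or on ratings made by someone who has been unmasked.
- Who holds the lists and when allocations are released are details that an article commonly leaves to the full protocol.

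All of this stands and limits the point to a risk. It does not rescue the sentence that links block size to blinding. Off-site generation hides the list, but does not remove the predictability that comes from a known, constant block.

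**Conclusion.** The point holds as a cheap improvement. The Bias section credits blocking with something that it cannot do, and the feature that it cites makes allocation easier to predict than varied blocks would. The figures of one third and 70.8% are exact for complete 1:1 blocks of four and a fully informed observer. For anyone who knows less, predictability is lower. They measure predictability only; no effect on the primary result has been estimated, and no direction of bias can be derived from the article. Selection bias and unmasking are possible consequences if information passes from therapists to recruiters or raters, but the article shows neither.

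**What to change.** Generate each home's sequence with randomly varying block sizes, for example 4, 6 and 8, and do not disclose the sizes to homes, therapists or assessors. Avoid blocks of 2: in a fixed block of 2 every second allocation is certain, and mixing in blocks of 2 gave the highest best-guess accuracy of the varied schemes. Public text need say only that block sizes vary at random.

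Rewrite the sentence in the Bias section so that assessor blinding rests on the placebo session (Interventions) and on keeping assessors apart from treatment (Outcome measures and Table 1), and describe blocking as a means of balancing arm sizes within homes.

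The cost is a set of new lists and a few words of text. Arm sizes within a home could differ by up to half the largest block, which is 4 patients with blocks of 8 against 2 with blocks of 4. The sample size does not change. The gain is mainly the removal of certain allocations; informed guessing would still do better than chance.

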### validity

The research will be conducted in four different nursing homes, that will enhance extrapolation of study findings. However, due to the fact that at least 4 different geriatric physical therapists will perform PMT and at least two different assessors of the severity of paratonia will participate, the internal validity may become compromised. A protocollized way of performing PMT and an extensive training of all therapists and assessors involved should ensure internal validity of this study and reliability of assessed outcomes.

The results of this randomised controlled trial will be published in a scientific journal and will be used for recommendations in the guideline of geriatric physical therapy and implemented in current physical therapy practice. This guideline will be developed according to method of clinical practice guideline development of the Royal Dutch Physiotherapy Association (KNGF) [21].
